## Abstract

**Introduction:**

Pakistan is one of the countries most affected by climate change, where peak temperatures in certain areas frequently exceed 40°C. Despite evidence that vernacular designs and behavioural adjustments can reduce indoor temperatures, heat‐adaptation efforts remain concentrated in urban or high‐resource settings, with limited evidence for vulnerable rural populations in low- and middle-income countries, including Pakistan.

**Methods and analysis:**

This trial aims to evaluate the effectiveness of a comprehensive Resilience and Heat Adaptation Bundle (ReHAB) that integrates behavioural and structural interventions to reduce heat-related morbidity and mortality and improve internal ambient conditions in rural settings of Pakistan. This study is a prospective, cluster-randomised trial, comprising 22 clusters allocated to intervention and control arms in a 1:1 ratio. The ReHAB intervention combines community education and awareness with targeted structural improvements, including roof and wall treatments, enhanced shading, improved ventilation, sustainable energy installations and communal outdoor shelters. Health and behavioural data will be collected through household surveys, while wearable devices and environmental sensors will measure individual heat exposure and record indoor and outdoor thermal conditions.

**Ethics and dissemination:**

The study has received ethical approval from the Aga Khan University (AKU) (ref: 2025–11559-35625) and National Bioethics Committee (ref: 4-87/NBCR-1065/23/1736). Written informed consent will be obtained from all participants before enrolment. Referral pathways to healthcare facilities will be established to ensure timely management of complications. Findings will be disseminated through peer-reviewed publications, scientific conferences and engagement with policymakers and public health stakeholders. Results will also be shared with participants and communities through meetings and informal sessions to raise awareness and support evidence-based heat adaptation.

**Trial registration number:**

NCT06983483.

Strengths and limitations of this studyThe trial will evaluate heat adaptation strategies involving structural housing modifications (retrofitting) and behavioural interventions in rural communities.The use of weather stations, environmental monitoring devices and personal wearable sensors will enable comprehensive measurement of household thermal environments, individual heat exposure, health outcomes and physiological responses.Strong community engagement and participatory implementation approaches are incorporated to enhance acceptability, local ownership and long-term sustainability of the interventions.Compliance challenges related to wearable devices, including potential discomfort during hot weather and inconsistent usage, may affect completeness of physiological monitoring data.

## Background

 Anthropogenic greenhouse gas emissions have raised global temperatures by approximately 1.1°C since the late 19th century^1^ and as a result, extreme heat events are becoming more frequent, prolonged and intense. Marine heatwaves have tripled in duration since the 1940s,^2^ while land-surface heatwaves have intensified, contributing to rising heat-related morbidity and mortality worldwide,^3^ with nearly 37% of heat-related deaths being attributed to climate change over the past two decades.^4^ A multicountry analysis across 732 locations in 43 countries suggested that mean temperatures had risen by 0.26°C per decade between 2000 and 2019, with heat-related mortality increasing proportionally.^5^ The most vulnerable populations are affected disproportionately; heat-related mortality among older adults increased by approximately 85% between 2000–2004 and 2017–2021.^6^ Extreme heat also reduces the quality of life by disrupting daily functioning, physical comfort, mobility and productivity, with downstream effects on economic stability and psychological well-being.^7^

Pakistan faces the compound challenges of climate change, poverty and infrastructure deficits. The country experiences recurrent heatwaves including the catastrophic 2015 heatwave, which resulted in approximately 700 deaths in Sindh,^8^ and the 2024 heatwave, during which temperatures in rural Sindh approached 50°C for several consecutive days and overwhelmed local health facilities with cases of heatstroke and gastroenteritis.^9^ Rural populations, many of whom are engaged in outdoor manual labour, face additional vulnerabilities as over 50% lack piped water and rely on hand-pumps or canals, while prolonged power outages limit access to fans, refrigeration and other cooling measures.^10
11^ Primary healthcare centres often lack basic facilities, which may delay treatment for heat-related illnesses and increase preventable morbidity and mortality.^12^

Historically, the rural communities adopted passive, low-cost strategies embedded in vernacular architecture, including use of mud, brick and stone construction, wind catchers, thermal mass, strategic building orientation, courtyards and shaded spaces. These approaches help to reduce indoor heat and maintain comfort without reliance on electricity.^13–15^ However, with time these indigenous practices are being replaced by concrete structures that are often poorly oriented for heat protection and ventilation. Improving the housing infrastructure is therefore important, alongside behavioural adaptations such as appropriate work-rest schedules, wearing loose cotton clothing and modifying food and fluid intake.

Although the recent heatwave management plans and early warning systems have improved emergency response, they primarily address acute exposure and do not sufficiently focus on preventive measures and reducing chronic household-level heat stress in resource-constrained rural communities. Most evidence on structural heat adaptation interventions comes from high-resource or urban settings.^16^ A few studies have evaluated simple community-level strategies including a community health worker-led education programme in Karachi that reduced unscheduled hospital visits,^17^ while agroforestry and tree-based interventions in rural low- and middle-income country (LMIC) settings have demonstrated modest health and economic benefits, although their health impacts remain underquantified.^18^

These gaps highlight the need for context-specific, low-cost heat adaptation strategies tailored to the rural socioeconomic and infrastructural realities. The Structural Heat Adaptation and Education in Rural Settings trial will evaluate one of the first heat adaptation and resilience bundles combining vernacular retrofits, community mobilisation and targeted behaviour change in rural context to generate evidence for scalable, community-led climate adaptation in a heat-vulnerable region.

## Methodology

### Objective

#### Primary

To assess the feasibility and effectiveness of a Resilience and Heat Adaptation Bundle (ReHAB) on heat-related health risks for vulnerable populations in rural settings of Pakistan.To assess the effectiveness of ReHAB on quality of life of vulnerable populations in rural settings of Pakistan.

#### Secondary

To evaluate the effectiveness of ReHAB on indoor heat in rural settings.To evaluate the impact of ReHAB on key physiological variables (sleep quality, heart rate, physical activity and energy expenditure) in adults residing in rural settings.

### Study setting

This study will be conducted in a representative rural district of Matiari which has a total area of 1417 square kilometres and a population of 849 383.^19^ It comprises three subdistrict administrative units (tehsils); Hala, Matiari and Saeedabad. Each tehsil is further divided into multiple union councils. During summer months, the average outdoor temperature usually ranges from 38°C to 42°C. The hottest period extends from May to August, with average daily maximum temperatures surpassing 50°C.^20^ The community residing in this setting belongs to a low socioeconomic background with limited access to basic amenities with agriculture and livestock as their main source of income.

### Study design

This study is a 2-year prospective, cluster-randomised controlled trial designed to evaluate the effectiveness of ReHAB intervention in rural settings. One village will serve as one cluster with 70–80 households randomized, and these clusters will be randomly assigned to either the intervention or control arm in a 1:1 ratio (figure 1). Due to the nature of the intervention, blinding of participants and researchers will not be feasible, but data analysis would be blinded. The trial is registered on clinicaltrial.gov with trial registration number NCT06983483. The study field activities will run from 1 January 2026 to 31 December 2027.

**Figure 1 F1:**
[figure not shown]
Study design diagram.

### Population

The population of this trial will include all members of the households within the selected clusters. A subset of eligible adults aged 18–60 years will be randomly selected for detailed physiological and personal heat exposure assessments.

### Exclusion criteria

We will exclude any clusters that present significant accessibility or security concerns, have inadequate structural stability for retrofitting or limited community cooperation. For the subset population, individuals unwilling to wear both (Fitbit and temp-u) devices simultaneously, individuals with cognitive or severe mental health conditions that may impair their ability to provide informed consent or comply with study procedures, and individuals with severe physical disabilities that would limit participation in physiological monitoring will be excluded.

### Outcomes

All primary, secondary and outcomes assessed for subset of population along with definitions are provided in table 1 and figure 2.

**Table 1 T1:** Outcomes

Primary outcomes	
Heat-related illness	Defined as a documented heat condition/illness according to the International Classification of Disease-11th Revision and institutional classification which classifies heat-related illness as heat stroke, heat syncope, heat exhaustion, heat fatigue, heat cramps and heat rash (figure 2).^30 31^
Quality of life	Quality of life would be assessed according to the WHOQOL-BREF* tool and assessed during two consecutive peak summer and winter seasons.

Secondary outcomes	
Health outcomes	
All-cause mortality	Defined as the total number of deaths in the study population over the study period
Hospital visit/hospitalisation	Defined as the number of hospital admissions (primary, secondary or tertiary facilities) during summers
Environmental outcomes	
Heat Index	Indoor heat index (temperature and humidity)^32^ measured through fixed weather devices
Universal Thermal Climate Index	Defined as a biometeorological index that describes the human body’s physiological response to the environment. It integrates air temperature, humidity, wind speed and radiant temperature to assess the overall thermal stress on the human body
Thermal comfort	Defined as change in the condition of mind that expresses satisfaction with the thermal environment
Outcomes measured for subset of population (individual level)	
Personalised heat exposure	Defined as mean daily external temperature each individual experiences (indoors and outdoors) as recorded by a wearable temperature monitor.
Heart rate	Defined as mean heart rate measurements (beats per minute) taken at 1-hour interval as recorded by wearable android device
Sleep quality	Defined as a biological process that alternates between non-rapid eye movement sleep and rapid eye movement sleep as recorded through a wearable android device
Physical activity	Defined as mean daily duration of sedentary, lightly active, moderately active and very active as measured using a wearable android device.
Energy expenditure	Defined as average total number of calories burned in a day recorded using a wearable android device.
Economic outcomes	
Cost-effectiveness	Measured as the difference in cost divided by the difference in health effect between the intervention and control groups

* WHO Quality of Life Brief tool.

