##### Community education and awareness

The educational component of ReHAB was developed based on findings from the formative phase, including systematic review, qualitative work, stakeholder consultations and pilot testing. Community mobilisation will be implemented throughout the intervention. Community groups (CGs) will be established across all 11 intervention clusters, with separate male and female representation. Each CG (6–8 members) will include local government representatives, elders, religious leaders and male and female community members. CGs will lead mobilisation activities and support surveillance of the primary outcome (heat illness).

Activities will include dissemination of heatwave warnings, awareness sessions and door-to-door outreach on heat-health practices (hydration, clothing and activity scheduling). CGs will maintain logbooks to record healthcare visits within their catchment areas and attendance in community meetings. Practical demonstrations of cooling strategies (eg, shade setup, light clothing, wet towels, misting and work–rest–shade cycles) will be conducted, supported by Information, Education and Communication (IEC) materials. This structured, behaviour-focused delivery aims to ensure both the uptake and sustainability of protective cooling practices. Community hydration measures (eg, temporary drinking water facilities) will also be implemented to reduce dehydration among outdoor workers.

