### Control arm

The control arm will receive routine care and usual public-sector health services and general government or media heat-related information which is available to the wider population with no additional intervention. Selected community representatives will conduct surveillance for heat-related illnesses.

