### Data collection from subset population

Monthly data will be collected from the subset population to provide detailed insights into heat stress and intervention effectiveness (table 3). This will include assessment of thermal comfort, mental health and heat exposure.

**Table 3 T3:** Schedule of outcome assessments and follow-up activities

Parameter	Time points	Details	Devices/tools	Population/unit
Primary outcomes				
All heat-related illness	Weekly during peak summers	Heat-related illnesses	Weekly community survey, health facility data, community surveillance	All members of included households
Quality of life	Mid of April, July and December for two consecutive years	Quality of life mean score	WHOQOL-BREF* questionnaire	Indexed adults of all included households
Secondary outcomes				
All-cause mortality	Weekly during peak summers	Any mortality occurring within the included clusters	Weekly community survey, health facility data, community surveillance	All members of included households
Hospital visit/hospitalisation	Weekly during peak summers	Any hospital admission or hospital visit occurring within the included clusters	Weekly community survey, health facility data, community surveillance	All members of included households
Indoor Heat Index	Continuous throughout the year	Indoor data loggers	Ibutton, Kestrel Drop D2, Temp-U	All included households
Thermal comfort (home)	Monthly	Self-reported comfort levels	Thermal comfort survey adapted from CHEQ-5‡	Indexed adults randomised for subgroup
UTCI	Continuous throughout summers	Outdoor only	Kestrel Drop D2, Kestrel 5400, HOBO weather station	Overall catchment area
Outcomes measured for subset of population				
Personalised heat exposure	Baseline, Monthly	Occupation, sun exposure, illness history, daily routine	Structured survey tool (adapted from HotHaps) and Temp-U	Indexed adults randomised for subgroup
Physiological strain markers	Continuous throughout summers	Heart rate, sleep cycles, VO₂ max†	Fitbit Inspire 3	Indexed adults randomised for subgroup

Participant compliance will be monitored through spot checks and periodic review of device data. For Fitbit devices, heart rate data will be reviewed, as prolonged absence of heart rate recordings may indicate that the device was not worn. Similarly, iButton and Temp-U data will be checked periodically for implausible temperature spikes or sudden drops, which may indicate non-compliance or incorrect device use.

* WHO Quality of Life Brief tool.

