#### Secondary outcome analysis

Secondary outcomes will be analysed within the same cluster randomised framework, accounting for clustering at the design level using mixed-effects models or generalised estimating equations as appropriate to the distribution of each outcome. All-cause mortality and hospital visits/hospitalisations, measured as counts or rare events, will be analysed using mixed-effects Poisson or logistic models (or Cox proportional hazards models where individual-level time-to-event data are available), with results reported as IRRs, risk ratios or HRs with 95% CIs. Indoor heat index and UTCI, both continuous environmental exposure measures, will be assessed using linear mixed-effects models with random intercepts for clusters and adjustment for temporal variation to estimate mean differences between trial arms. Thermal comfort, measured either as a continuous score or ordinal response, will be analysed using linear mixed models or ordinal logistic mixed-effects models depending on scale properties. Subgroup analyses will be conducted by including interaction terms between intervention assignment and key effect modifiers such as age (Women of reproductive age, children and elderly), sex and occupational exposure. All models will be adjusted for relevant covariates where appropriate, and robustness will be assessed through sensitivity analyses including alternative correlation structures. Cost-effectiveness analysis will be conducted to evaluate the economic feasibility of different adaptation strategies.

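### The hospital outcome is defined as admissions in Table 1 but as admissions or visits in Table 3 and the analysis text, and its sources are not explicitly limited to those collected alike in both arms

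*Protocol article*

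**What the plan says.** The hospital outcome appears in three places in the protocol article.

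- **Outcomes, Table 1.** The row label names both hospital visits and hospitalisation. The definition beside it covers admissions only: "Defined as the number of hospital admissions (primary, secondary or tertiary facilities) during summers".
- **Table 3 (schedule of assessments).** The row for the same outcome reads "Any hospital admission or hospital visit occurring within the included clusters". Its sources are given as "Weekly community survey, health facility data, community surveillance", without distinguishing the arms, and its unit is the members of the included households.
- **Secondary outcome analysis.** Visits and hospitalisations are taken together: "All-cause mortality and hospital visits/hospitalisations, measured as counts or rare events, will be analysed using mixed-effects Poisson or logistic models".

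On who records what, the Community education and awareness section says "Community groups (CGs) will be established across all 11 intervention clusters, with separate male and female representation", and then "CGs will maintain logbooks to record healthcare visits within their catchment areas and attendance in community meetings". The surveillance task it names for these groups is the primary outcome, heat illness. For the other arm, the Control arm section says "Selected community representatives will conduct surveillance for heat-related illnesses" and describes no log of healthcare visits. The Household data collection section places the baseline, periodic and endline surveys in all 22 clusters. It also says that reported facility visits will be checked against facility records where feasible, in a paragraph about heat-related illness.

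**The concern.** Two readers could follow this article faithfully and analyse different outcomes. One would count admissions, as the Table 1 definition says. The other would count admissions plus visits, as Table 3 and the analysis section say. If visits are the more frequent event, the combined count is close to a visit count, and an effect on admissions could be nearly invisible in it. If the definition is settled only after data are seen, the reported result can depend on which one is chosen.

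The second issue is ascertainment. Community surveillance is a listed source for this outcome. In the intervention arm the groups that support surveillance also keep logbooks of healthcare visits, and no equivalent is described in the control arm. The Study design section says that participants and researchers are not blinded. If logbook entries were allowed to add events, the intervention arm would have one more route by which an event could be found. That would push the comparison against the intervention.

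**Working it through.** **Step 1. The definitions side by side.**

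| Place | Admissions counted | Visits counted |
|---|---|---|
| Table 1, row label | yes | yes |
| Table 1, definition | yes | no |
| Table 3, details | yes | yes |
| Secondary outcome analysis | yes | yes |

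The Table 1 definition is the outlier and conflicts with its own label. This needs no assumption. It is a contradiction in the current text, not a detail left to a fuller document.

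**Step 2. The sources by arm.**

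| Source | Intervention | Control |
|---|---|---|
| Periodic household surveys | described | described |
| Health facility data | listed, arms not distinguished | listed, arms not distinguished |
| Community surveillance | community groups, stated task heat illness | community representatives, stated task heat illness |
| Logbook of healthcare visits | described | not described |

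The logbook is the only item described for one arm alone. It is not named as a source for the hospital outcome, and nothing in the article expressly keeps it out.

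**Step 3. What the choice of definition could do.** The article gives no rate, power or effect size for this outcome, so there is no figure to reproduce. The inputs below are assumptions. Let r be visits per admission in the control arm, a the rate ratio for admissions and v the observed rate ratio for visits. Then

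combined rate ratio = (a + r·v) / (1 + r).

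Take r from 5 to 20.

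- Admissions fall 30%, visits unchanged (a = 0.70, v = 1.0): (0.70 + 5)/6 = 0.950 and (0.70 + 20)/21 = 0.986.
- Admissions fall 30%, visits rise 10% (a = 0.70, v = 1.1): (0.70 + 5.5)/6 = 1.033 and (0.70 + 22)/21 = 1.081.

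**Step 4. What unequal capture could do, if the logbooks added events.**

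- No true effect, visit capture 10% to 30% higher in the intervention arm only (a = 1, v = 1.1 to 1.3). The lowest value is (1 + 5 × 1.1)/6 = 1.083 and the highest is (1 + 20 × 1.3)/21 = 1.286.
- In a simpler form that applies to either count, observed rate ratio = true rate ratio × (intervention capture / control capture). With control capture assumed at 80% and intervention capture at 85%, 90% or 95%, the multiplier is 85/80 = 1.06, 90/80 = 1.13 or 95/80 = 1.19. A true 0.70 would then appear as 0.74, 0.79 or 0.83.
- If the logbooks are not a source, they add nothing and the multiplier from this cause is 1.00.

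**The case against.** The strongest reply is that no ascertainment bias is written into the plan. The logbooks are mentioned once, in the same sentence as meeting attendance, which reads naturally as process recording. Table 3 names three sources and logbooks are not among them. The surveys run in all 22 clusters. The Control arm section does not say that its representatives record heat illness and nothing else. All of this stands. A reader might infer that counting visits necessarily brings in intervention-only records and so biases the comparison, but the article does not support that. What remains is a conditional risk.

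A reader might also infer that an admissions-only definition would remove the risk. The article does not support that either. Its one sentence on verification concerns reported visits, is limited to where feasible, and sits in the heat-illness text. A logbook of healthcare visits could also bring admissions to light.

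Two further replies are fair. If education changes how often people seek care, that is an effect of the intervention on visits and not a measurement error. The Background cites an education programme that reduced unscheduled hospital visits, so the 10% rise in Step 3 is only a scenario and the opposite direction is just as possible. And Table 3's reference to events occurring within the clusters might seem to exclude care at distant facilities, but the unit in the same row is the members of included households, which answers it.

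None of these replies touches the conflict between the Table 1 definition and the other places.

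**Conclusion.** The contradiction is certain: one secondary outcome carries two incompatible definitions. The ascertainment point holds only conditionally: if logbooks kept in intervention clusters alone contribute events, capture differs by arm, for admissions and visits alike, in the direction unfavourable to the intervention.

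The size is unknown. The rate ratios shown rest wholly on assumed visit-to-admission ratios, capture levels and effects, and illustrate direction and plausible scale only. The matter is worth correcting but limited in reach: the sample size and the fixed-sequence tests of the two co-primary outcomes do not depend on it.

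**What to change.** Make the Table 1 definition, the Table 3 row and the secondary outcome analysis agree. The preferable form is two separately labelled counts among members of included households, one of hospital admissions and one of outpatient visits, each analysed on its own. This keeps visits, which most of the text clearly intends, and lets an effect on admissions be seen.

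Add one sentence saying that only events from sources collected identically in both arms count towards either outcome, namely the weekly survey and facility records, and that the community-group logbooks are used for process monitoring.

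The cost is a change of wording in two tables and the analysis text. The small downside is that admissions alone give fewer events than a combined count, so that estimate will be less precise.
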